### Sample size

2.4

This study is a randomized controlled trial. The experimental group is basic treatment (health education and Tiotropium bromide) + Baduanjin exercise training, and the control group is basic treatment + maintain the original lifestyle and control the exercise. Pulmonary function (FEV_1_%) is the main outcome index. According to previous literature.^[19]^ The mean and standard deviation of FEV_1_% of the control group was 57.09 and 22.53, while the mean and standard deviation of FEV_1_% of the experimental group was 60.24 and 20.15, set *α* = 0.05 (bilateral), *β* = 0.10. The sample size N1 = N2 = 77 cases of experimental group and control group were calculated by Power Analysis and Sample Size version 15.0.5 (PASS 15.0.5 NCSS, LLC USA). Assuming a 20% dropout rate for the study subjects, 96 samples were needed. Therefore, the lowest sample size was 192.

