### Eligibility criteria

2.8

Inclusion criteria:

(1)Age range 40 to 70 years, men or women;(2)Mild COPD defined by GOLD guidelines: FEV_1_/FVC <70% and FEV_1_ ≥80% predicted value;(3)In the stable phase of COPD, no respiratory infections and acute exacerbations of COPD in the past 4 weeks;(4)Have not performed Baduanjin and similar Qigong exercises in the past;(5)Volunteer to take part in research and provide informed consent.

Exclusion criteria:

(1)Patients with chronic lung diseases (such as bronchial asthma, interstitial lung disease, active tuberculosis, or bronchiectasis) need intervention or treatment;(2)Patients suffering from severe primary diseases (such as severe mental illness) diseases, cardiovascular and cerebrovascular diseases, liver and kidney diseases, endocrine diseases, hematopoietic diseases, malignant tumors, etc;(3)Patients with limited physical activity or other reasons who cannot perform Baduanjin training;(4)The patient has participated in any other clinical studies in the past 6 months.

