### Outcome measures

3.2

Primary outcome: The primary outcome is the change in lung function from baseline to the end of the follow-up period (all time points). Including FEV_1_, FVC, FEV_1_/predicted value.

Secondary outcomes: Including COPD assessment test (CAT), 6 minute walking test (6MWT), dyspnea score (modified British medical research council dyspnea score, mMRC), and St. George Respiratory Questionnaire (SGRQ), Self-rating Depression Scale (SDS), Self-rating Depression Scale (SAS).

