## Discussion

4

COPD is a major public health problem that seriously affects the quality of life of patients, even life-threatening. The sign of COPD progression is decreased lung function, and pulmonary rehabilitation has been proven to be the most effective treatment strategy for improving shortness of breath, health status, and quality of life.^[13]^ However, traditional pulmonary rehabilitation requires a series of professional evaluations to develop a perfect and personalized plan,^[22]^ so the overall effect is not satisfactory, and it is urgent to develop family-based pulmonary rehabilitation methods.^[23]^ Baduanjin is the representative of the traditional Chinese medicine guidance method, covering endurance training, breathing muscle training, stretching training, and psychological adjustment required for pulmonary rehabilitation. The whole set of movements is easy to learn, moderate intensity, and significant efficacy, which applicability and cost are much better than traditional pulmonary rehabilitation. However, previous studies have mostly focused on the efficacy of Baduanjin in the middle and late stages of COPD, and there is no unified understanding of its intervention effect in mild COPD pulmonary function decline. Therefore, this study focuses on the effect of Baduanjin on lung function in the early stage of COPD.

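### The FEV1% values used for the sample size fit neither the mild-COPD patients who may enrol nor the change-from-baseline endpoint, so the stated 90% power is unsupported

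*Protocol article*

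**What the plan says.** Section 2.4 (Sample size) says that pulmonary function, written as FEV1%, "is the main outcome index". It takes two pairs of planning values from one earlier publication: the mean and SD "of the control group was 57.09 and 22.53", and the mean and SD "of the experimental group was 60.24 and 20.15". The error rates are alpha "0.05 (bilateral") and beta "0.10. The sample size N1 = N2 = 77 cases" per group, raised to 96 per group and 192 in total for 20% dropout. The section does not define FEV1% or give the time point of the literature values.

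Section 2.8 (Eligibility criteria) admits only mild COPD: FEV1/FVC below 70% and FEV1 "≥80% predicted value".

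Section 3.2 (Outcome measures) states: "The primary outcome is the change in lung function from baseline to the end of the follow-up period (all time points").

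The Discussion says that "previous studies have mostly focused on the efficacy of Baduanjin in the middle and late stages of COPD", and describes this trial as, to the authors' knowledge, the first of Baduanjin in mild COPD.

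**The concern.** A sample-size calculation needs a difference and an SD that apply to the patients who will enrol and to the quantity that will be compared. Section 2.4 meets neither condition on its face.

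- **Population.** A patient at either planning mean could not be randomised if FEV1% is percent predicted. Restricting entry to FEV1 of at least 80% also narrows the spread, so an SD above 20 cannot be carried over.
- **Scale.** Values of 57 and 60 are levels, not changes. The SD of a change depends on the correlation between baseline and follow-up, which the section does not give.

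At stake is the stated 90% power, on which a reader would rely when interpreting a null result. Nothing in the article shows what power 192 patients give for the endpoint as defined.

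**Working it through.** **Inputs.** From section 2.4: means 57.09 and 60.24, SDs 22.53 and 20.15, two-sided alpha 0.05, power 0.90, 77 per arm (96 after dropout). From section 2.8: FEV1 at least 80% predicted and FEV1/FVC below 70%. Normal distributions and all SDs of change are assumptions made here; the article gives neither.

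**1. The plan's own figure.** Difference = 60.24 − 57.09 = 3.15. Pooled SD = √((22.53² + 20.15²)/2) = 21.37. Then n per arm = 2 × (1.960 + 1.282)² × 21.37² / 3.15² ≈ 968 (969 with the t distribution), not 77. Using either single SD, 80% power, one-sided testing or a one-sample form does not give 77 either. At a difference of 3.15, 77 per arm gives 90% power only if SD = 3.15 / (3.242 × √(2/77)) ≈ 6.0, a value that section 2.4 does not state. This is a separate fault; it matters here because correcting it alone would leave the inputs unsuitable.

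**2. FEV1% read as percent predicted.**
- Distance below the entry floor: 80 − 57.09 = 22.91 and 80 − 60.24 = 19.76 points.
- Share at or above 80: 1 − Φ(22.91/22.53) = 1 − Φ(1.017) = 15.5%; 1 − Φ(19.76/20.15) = 1 − Φ(0.981) = 16.3%.
- SD among those at or above 80, from s × √(1 + aλ − λ²) with a = (80 − mean)/s and λ = φ(a)/(1 − Φ(a)): a = 1.017 and λ = 1.539 give 10.0; a = 0.981 and λ = 1.510 give 9.0.

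**3. FEV1% read as FEV1/FVC.** Share above the 70% ceiling: 1 − Φ((70 − 57.09)/22.53) = 1 − Φ(0.573) = 28%; 1 − Φ((70 − 60.24)/20.15) = 1 − Φ(0.484) = 31%. The values fit the eligibility criteria poorly on this reading too.

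**4. Level against change.** Under randomisation the expected baseline difference is zero, so the expected group difference is the same for follow-up level and for change. With equal variances, SD of change = SD of level × √(2(1 − r)), where r is the baseline-to-follow-up correlation. The two SDs are equal only at r = 0.5; above that, the SD of change is the smaller.

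**5. Power of the fixed sample for 3.15 points** (two-sided 0.05, noncentral t, noncentrality 3.15 / (SD × √(2/n))):

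| Assumed SD of change | 77 per arm | 96 per arm |
|---|---|---|
| 6 | 90% | 95% |
| 8 | 68% | 77% |
| 10 | 49% | 58% |
| 12 | 37% | 44% |

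The 77 column takes only completers after 20% dropout. The 96 column takes everyone randomised, as the intention-to-treat analysis with last observation carried forward in section 3.6 would.

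**6. How plausible is the SD range?** With a level SD of 9 to 10 from step 2 and equal variances, r = 1 − SD_change² / (2 × SD_level²). An SD of change of 6 corresponds to r of about 0.78 to 0.82, 8 to about 0.60 to 0.68, 10 to about 0.38 to 0.50, and 12 to about 0.11 to 0.28. The last row is therefore an extreme case.

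**The case against.** The best defence is that the direction of harm is not established. The mild slice has a smaller SD than the planning values, and a change score with a correlation above 0.5 has a smaller SD still. Both push the required sample down for a given difference, and at an SD of change near 6 the trial has the power it claims. Comparing follow-up levels is also legitimate in a randomised trial, and section 3.6 does not confine the group t test to changes. All of this stands. It does not rescue the stated power, because the favourable SD appears nowhere in the article and the SDs that do appear belong to a different spread of patients.

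Some stronger readings are tempting but are not supported:

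- **That the source patients were all of a severity this trial excludes.** The cited publication is not shown, the Discussion says only that earlier work was mostly in later stages, and the SDs imply that a minority were mild.
- **That the inputs are end-of-study values.** Section 2.4 gives no time point; it is clear only that they are levels.
- **That level inputs say nothing about the endpoint.** The expected difference carries over; only the SD does not.
- **That 3.15 points would mean abolishing much of the expected decline.** The Introduction's 47 to 79 mL/yr is for GOLD II, which this trial does not enrol. For GOLD I it says only that decline is fastest, with no rate.

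It may also be said that repairing the arithmetic would already force section 2.4 to be rewritten. The edits overlap, but a correct sum on the present inputs would still describe the wrong patients.

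**Conclusion.** The concern holds in this form: the planning values in section 2.4 do not match the eligibility criteria in section 2.8 on either reading of FEV1%, and their SDs are not those of the primary outcome in section 3.2. The stated 90% power is unsupported for the enrolled population and endpoint.

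The mismatch in location, 20 to 23 points below the entry floor, follows directly from the document if FEV1% is percent predicted. The 15% to 16% qualifying share, the slice SD of 9 to 10 and the 28% to 31% above the FEV1/FVC ceiling rest on normality. The power range, 37% to 90% with 77 per arm or 44% to 95% with 96, rests on assumed SDs of change from 6 to 12 and on keeping 3.15 points as the target, although that difference also comes from the same literature values.

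A reader might infer that the trial is certainly underpowered. The document does not show that: the power is unknown, and it is adequate at the low end of the assumed SDs.

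**What to change.** Rewrite section 2.4, leaving the sample at 192:

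1. Define FEV1% explicitly as percent predicted or as FEV1/FVC.
2. Replace the planning values with an SD of change in FEV1 percent predicted for patients with FEV1 of at least 80% predicted, with its source. If none is available, state an assumed range and label it as such.
3. Report the power that the fixed sample gives across that range, saying whether it is for 77 completers or all 96 per arm, in the manner of the table above.
4. Make the calculation traceable, so that the stated number follows from the stated inputs.

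The cost is a redrafted section and a stated power that is probably less favourable than 90%. No patients or visits are added.

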### Design

2.1

This study is a randomized, parallel, and controlled trial designed to evaluate the effectiveness of Baduanjin exercise intervention in improving lung function, exercise capacity, and quality of life in patients with mild COPD. A total of 192 patients will be recruited in Chengdu and randomly assigned to the experimental group or the control group in a 1:1 ratio. Participants in the experimental group will receive a 24-week Baduanjin exercise training intervention at least 5 days a week and 60 minutes a day, while participants in the control group will not be given any specific exercise intervention and will be told to maintain their original lifestyle for 24 weeks. The primary and secondary outcomes will be measured at baseline and at weeks 12, 24, 36, 48, 72, and 96. The participation process of this trial is shown in Fig. 1. This agreement follows the standard agreement item: Intervention Test Recommendation (SPIRIT) guidelines,^[20]^ and meets the SPIRIT list (please see Guidelines Checklist). The study flow chart is presented in Fig. 2.

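### The stated inputs require about 968 patients per arm, not 77; on those inputs the trial has about 15% power, not 90%

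*Protocol article*

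**What the plan says.** Section 2.4 (Sample size) of the protocol article says that FEV1% "is the main outcome index". From an earlier study it takes the mean and SD of FEV1% in each group: that "of the control group was 57.09 and 22.53" and that "of the experimental group was 60.24 and 20.15". It sets a two-sided alpha of 0.05 and a beta of 0.10, that is, 90% power. It then reports: "The sample size N1 = N2 = 77 cases of experimental group and control group were calculated by Power Analysis and Sample Size". The allowance for loss follows: "Assuming a 20% dropout rate for the study subjects, 96 samples were needed", giving 192 in total. Section 2.1 confirms equal allocation: patients are "randomly assigned to the experimental group or the control group in a 1:1 ratio".

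The paragraph gives no other input: no SD of change, no correlation between baseline and follow-up, no covariate adjustment and no repeated-measures structure. For measurement data, section 3.6 plans a two-group t test or a non-parametric test.

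**The concern.** All the inputs of a two-mean sample size calculation are printed, so the result can be checked directly. A difference of 3.15 points with SDs above 20 is a very small standardised effect, and 77 per arm is far too few to detect it with 90% power.

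This is the calculation for the primary outcome. If the 90% is wrong, a non-significant result could be taken as evidence that Baduanjin does not slow lung function decline, when the design had little chance of showing the planned effect. A significant result from a trial with such low power would probably overstate the effect. Participants are asked for 24 weeks of training and assessments up to week 96 partly on the strength of this justification.

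**Working it through.** **Inputs (protocol article, section 2.4; allocation from section 2.1).** Control mean 57.09, SD 22.53. Experimental mean 60.24, SD 20.15. Two-sided alpha 0.05 (z = 1.960). Power 90% (z = 1.2816). Allocation 1:1. Dropout 20%.

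**Effect size**
- Difference: 60.24 − 57.09 = 3.15
- Root-mean-square SD: √[(22.53² + 20.15²)/2] = √(913.62/2) = 21.37
- Standardised difference: 3.15/21.37 = 0.147

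**Attempt to reproduce 77**

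n per arm = (1.960 + 1.2816)² × (22.53² + 20.15²) / 3.15² = 10.51 × 913.62 / 9.92 = 967.5, so 968. The noncentral t calculation gives 968.4, so 969; Welch's version also gives 969. The ratio to the stated figure is 968/77 = 12.6.

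**Variants, in case a different setting was used** (normal approximation)

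| Setting | n per arm |
|---|---|
| Two-sided, 90% power, smaller SD only (20.15) | 860 |
| Two-sided, 90% power, larger SD only (22.53) | 1,076 |
| One-sided, 90% power | 789 |
| Two-sided, 80% power | 723 |
| One-sided, 80% power | 570 |
| One-sided, 80% power, smaller SD | 506 |
| One-sample formula | 484 |
| Beta of 0.10 entered as the power | 43 |

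None gives 77.

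**Power at the planned size** (noncentral t, difference 3.15, SD 21.37)
- 77 per arm: standard error = 21.37 × √(2/77) = 3.44; power 14.9%
- 96 per arm, no dropout: power 17.4%

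**What the planned size can detect at 90% power** (SD 21.37)
- 77 per arm: 0.5257 × 21.37 = 11.2 points
- 96 per arm: 10.1 points
- Half-width of the 95% confidence interval at 77 per arm: about 6.8 points, more than twice 3.15

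**What would make 77 correct**
- SD needed: 3.15/0.5257 = 5.99, about 6.0
- If this is the SD of change and the raw SD is 21.37, then 5.99² = 2 × 21.37² × (1 − r), so r = 0.96. Baseline adjustment by ANCOVA, 5.99² = 21.37² × (1 − r²), also gives r = 0.96.

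**Dropout**

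77/0.80 = 96.25, which rounds up to 97 rather than 96. With 96 randomised per arm, 96 × 0.80 = 76.8 remain. This difference is trivial.

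**The case against.** The strongest reply is that 15% is the power of an unadjusted comparison of raw FEV1% with SD 21.37, which may not be the comparison that matters. Section 3.2 defines the primary outcome as change from baseline, and the SD of change is usually smaller than the raw SD. The source values may also describe different patients: section 2.8 requires FEV1 of at least 80% of predicted, while the means used are 57.09 and 60.24. A sample restricted in that way need not have an SD of 21.4. If the SD of the analysed quantity is assumed to be 6, 8, 10 or 12, power for 3.15 points with 77 per arm is about 90%, 68%, 49% or 37%.

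Part of this stands. The true power of the trial is unknown, and the figures of 15%, 11.2 points and 6.8 points hold only on the printed inputs. It does not rescue the calculation. Section 2.4 presents the raw means and SDs as the basis for 77 and gives no SD of change or correlation, and section 3.6 names only group tests without baseline adjustment. If a smaller SD was in fact used, the printed inputs are not the basis of the calculation and the paragraph still has to be corrected.

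The rounding of 96.25 to 96 is too small to matter and is not part of the case for a correction.

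**Conclusion.** The concern holds. The stated sample size does not follow from the stated inputs: they require 968 per arm (969 by t test), against 77 reported. On those inputs the trial has 14.9% power at 77 per arm and 17.4% at 96 per arm, not 90%. This rests on a two-group comparison of means with equal allocation, two-sided alpha 0.05 and the printed means and SDs, and on nothing from outside the document. How 77 arose cannot be established from the article. Only an unstated SD of about 6.0 would support it. The error concerns the sizing of the primary outcome and must be corrected.

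**What to change.** Rewrite section 2.4 and keep 192 patients.

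1. **Preferred:** re-base the calculation on the SD of the quantity to be analysed, for example baseline-adjusted change in FEV1%. State that SD and its source, and make sure that section 3.6 describes the matching analysis. Give the difference detectable with 77 evaluable per arm at 90% power over a plausible range. For SDs of 5 to 12 (an assumed range) it is 0.5257 × 5 = 2.6 to 0.5257 × 12 = 6.3 points. If 3.15 points is kept as the target, say that it requires an SD of about 6.0.
2. **Otherwise:** keep the printed inputs and state plainly that 77 evaluable per arm gives about 15% power for 3.15 points at SD 21.4, and 90% power only for about 11.2 points.

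In either case, note that 192 randomised with 20% dropout leaves 76.8 per arm. There is no need to raise the total for rounding.

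The cost is one rewritten paragraph, a less favourable statement of power, and the renewed ethics approval that section 2.2 requires for any protocol amendment. If option 1 brings in baseline adjustment, section 3.6 needs a matching sentence. No extra patients are needed.

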### Randomization and allocation concealment

2.5

Members of the Sichuan Evidence-based Medicine Center of Traditional Chinese Medicine will use SAS 9.2 software (SAS, Cary, NC) to generate 192 random serial numbers. The grouping and treatment plan will be placed in an envelope made of carbon-free carbon paper and numbered in random serial numbers. And will be kept by an administrator who is not involved in recruitment and subsequent experiments. After signing the informed consent and receiving the baseline assessment of the primary and secondary outcome measures, the administrator will open the envelope in turn and provide the group number to the eligible participants. Finally, all participants will be randomly divided into the experimental group or the control group at a ratio of 1:1.

### Blinding

2.6

Due to the particularity of sports training, the participants, coaches, and follow-up personnel cannot be blinded, we will blind the result assessors through the following methods to ensure the reliability of the results. The results will be evaluated by a new person not involved in the previous experiment. Participants, sports coaches, and research assistants will be advised not to disclose any information about the assignment before the outcome evaluation begins. Therefore, the outcome evaluator will not know the assignment of the protocol until the end of the study.

### Diagnostic criteria

2.7

All participants must meet the Western medicine diagnostic criteria for COPD^[3]^ (Table 1) and Classification of airflow limitation severity in COPD (based on post-bronchodilator FEV_1_)^[3]^ (Table 2).

**Table 1 T1:**

Diagnostic criteria for chronic obstructive pulmonary disease^[3]^.

**Table 2 T2:**
[figure not shown]
Classification of airflow limitation severity in COPD (based on post-bronchodilator FEV_1_)^[3]^.

### Eligibility criteria

2.8

Inclusion criteria:

(1)Age range 40 to 70 years, men or women;(2)Mild COPD defined by GOLD guidelines: FEV_1_/FVC <70% and FEV_1_ ≥80% predicted value;(3)In the stable phase of COPD, no respiratory infections and acute exacerbations of COPD in the past 4 weeks;(4)Have not performed Baduanjin and similar Qigong exercises in the past;(5)Volunteer to take part in research and provide informed consent.

Exclusion criteria:

(1)Patients with chronic lung diseases (such as bronchial asthma, interstitial lung disease, active tuberculosis, or bronchiectasis) need intervention or treatment;(2)Patients suffering from severe primary diseases (such as severe mental illness) diseases, cardiovascular and cerebrovascular diseases, liver and kidney diseases, endocrine diseases, hematopoietic diseases, malignant tumors, etc;(3)Patients with limited physical activity or other reasons who cannot perform Baduanjin training;(4)The patient has participated in any other clinical studies in the past 6 months.

### Termination and withdrawal criteria

2.9

All participants will be informed of their right to withdraw from the trial and, if so, will receive standardized treatment. The reasons for the withdrawal will be recorded in their case report file (CRF). The criteria for stopping treatment and pulling patients out of the study are:

Participants have experienced exercise-related adverse events, and the researchers believed that they are unfit to exercise;Participant has another serious illness and needs to be treated during the study;The participant has suffered a severe exacerbation;Poor compliance so that exercise time is <80% of the prescribed time;Perform other pulmonary rehabilitation exercises during the study.

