#### Control group

3.1.2

The control group members will not receive any training while undergoing basic treatment, and they will be told to maintain the original lifestyle and control the amount of exercise. At the same time, each participant will be issued a daily activity record card to record the number of daily WeChat steps and additional activities.

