### Compliance

3.3

In this trial, compliance was quantified by participation in collective training and exercise book recording. The researchers will make every reasonable effort to follow the patients during the study. Messages will be sent via WeChat or over the phone at each training and follow-up session. Patients with a total time of >80% recorded in the collective training and exercise card will be considered as compliant.

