### Statistical analysis

3.6

All data analysis will be carried out in accordance with the principle of intentional processing. The missing value will be substituted for the last observation carried forward method. Before the analysis, 2 similar participants with complete data will be carefully checked to ensure that the data are correct.

The data will be analyzed using a social science version 22.0 statistical software packages (SPSS 22.0, Chicago, IL). The analysis method will be selected according to the distribution characteristics of the data: the measurement data will be checked using group *t* test or non-parametric test, the count data will be tested using chi-square test or Fisher exact probability method, and the score data will be tested using non-parametric test. Compared with the baseline value, paired *t* test or non-parametric test will be used to evaluate measurement data, and non-parametric test will be utilized to test count data. All statistical tests will be bilateral tests, and a *P* value <.05 will be deemed to indicate statistical significance.

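### The below-80% exercise rule ends study participation, not just training, and can act only in the Baduanjin arm, which conflicts with the intention-to-treat principle

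*Protocol article*

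**What the plan says.** Section 2.9 introduces a single list with the words "The criteria for stopping treatment and pulling patients out of the study are". The list includes "Poor compliance so that exercise time is <80% of the prescribed time", "The participant has suffered a severe exacerbation" and "Perform other pulmonary rehabilitation exercises during the study". It makes no distinction between stopping the intervention and ending outcome measurement.

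Section 2.1 states that the experimental group "will receive a 24-week Baduanjin exercise training intervention at least 5 days a week and 60 minutes a day". Section 3.1.2 states: "The control group members will not receive any training while undergoing basic treatment". Outcomes are scheduled at baseline and at weeks 12, 24, 36, 48, 72 and 96 (section 2.1), and the primary outcome covers all time points (section 3.2).

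Section 3.3 promises every reasonable effort to follow patients and uses the same 80% threshold to classify them: "Patients with a total time of >80% recorded in the collective training and exercise card will be considered as compliant". Section 3.6 states: "All data analysis will be carried out in accordance with the principle of intentional processing". This can only sensibly be read as intention-to-treat. The same section fills missing values by last observation carried forward (LOCF).

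**The concern.** Intention-to-treat needs outcomes on everyone randomised, whether or not they adhered. A rule that takes patients out of the study for not adhering prevents those outcomes from being collected. Here it can do so in one arm only. After the first 2 weeks training is mainly at home (section 3.1.1), so shortfalls against the prescribed time are foreseeable, and patients who fall short may differ in prognosis from those who do not.

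The randomised comparison is at stake. Measured Baduanjin outcomes to week 96 would come from patients who kept to the programme, while control outcomes would come from controls of every kind. Data that were never collected cannot be recovered at analysis.

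**Working it through.** **1. The passages side by side.**
- Section 2.9: exercise time under 80% leads out of the study.
- Sections 2.1 and 3.1.1: prescribed time exists for Baduanjin (60 minutes, at least 5 days a week, 24 weeks).
- Section 3.1.2: controls get no training. They keep a daily activity record, but have no prescribed time to fall short of. No control can meet the criterion.
- Section 3.3: the threshold classifies compliance, and patients are to be followed.
- Section 3.6: analysis as randomised, LOCF for gaps.

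Sections 2.9, 3.3 and 3.6 cannot all be carried out as written on measured data. A patient withdrawn during the 24-week programme loses at least 96 − 24 = 72 weeks of planned follow-up.

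**2. Size if withdrawn patients stay in the analysis through LOCF.** The plan gives no figure for withdrawals under this rule, only one overall dropout rate of 20% in section 2.4, so there is no stated value to reproduce. Inputs:
- FEV1 decline of 47 to 79 mL/yr: section 1, cited for GOLD II. The trial enrols GOLD I (section 2.8), for which no numeric rate is given. Its use here is an assumption.
- Last observed value at week 12 or 24: scheduled visits.
- Fraction f of the Baduanjin arm withdrawn for compliance, 10 to 30%: assumption.
- Straight-line decline, the same in withdrawn patients and others: assumption.

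Decline omitted per withdrawn patient by week 96 = rate × (96 − w)/52.18, where w is the week of the last value. Shift in the arm mean = f × that amount.

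| Rate (mL/yr) | Frozen at week | Omitted per patient (mL) | Shift, f = 10% | f = 20% | f = 30% |
|---|---|---|---|---|---|
| 47 | 24 | 64.9 | 6.5 | 13.0 | 19.5 |
| 47 | 12 | 75.7 | 7.6 | 15.1 | 22.7 |
| 79 | 24 | 109.0 | 10.9 | 21.8 | 32.7 |
| 79 | 12 | 127.2 | 12.7 | 25.4 | 38.2 |

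For example, 47 × 72/52.18 = 64.9 mL, and 10% of that is 6.5 mL; 79 × 84/52.18 = 127.2 mL, and 30% of that is 38.2 mL. The controls have no matching shift from this rule. At visits before week 96 the shift is smaller.

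**3. Size if withdrawn patients were left out instead.** Adherent Baduanjin patients would then be compared with all controls. Suppose there is no true effect, adherence and outcome correlate at r = 0.3 (assumed), and the least adherent fraction f of one arm is dropped. The bias in SD units is r × φ(z_f)/(1 − f), where z_f is the f-quantile of the standard normal distribution. With f = 20%: 0.3 × 0.280/0.8 = 0.105 SD. The standard error is √(1/76.8 + 1/96) = 0.153, and the two-sided type I error is 10.5% instead of 5%. For f = 10% and 30% it is 6.8% and 15.5%. At r = 0.1 the range over the same fractions is 5.2 to 6.1%, so this result depends heavily on the assumed correlation.

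**The case against.** **Analysis as randomised remains possible.** Section 3.6 covers all data analysis and supplies LOCF, so nothing says that withdrawn patients are deleted. This stands. A reader might infer from section 2.9 that non-adherers vanish from the comparison, but the text shows only that their measurement ends. Step 3 is therefore the less likely reading. What remains is an intention-to-treat analysis in name, run on frozen values for non-adherers in one arm.

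**Other criteria act in both arms.** A reader might infer that the severe-exacerbation and other-rehabilitation rules also select against one arm. The documents do not support that. Both are worded without restriction to an arm, controls could meet either of them, and the imbalance is unknown and could go either way. They still end follow-up for reasons tied to outcome or behaviour.

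**The direction is not certain.** The trial also aims to improve lung function. If it rises early, a value frozen before the improvement would work against Baduanjin. This stands, and the 6.5 to 38 mL holds only if the frozen values omit decline.

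**Section 3.3 promises follow-up.** It does, but a general promise of effort does not override an explicit criterion for leaving the study. It is one more section to reconcile.

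**Part of the harm belongs to LOCF.** That is fair, and the choice of imputation is a separate matter. This point is that the rule itself creates the missing data, unequally between arms. A better imputation method would not replace the lost measurements.

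**Conclusion.** Wrong as written. Section 2.9 ends study participation for low exercise time, this can happen only in the Baduanjin arm, and it conflicts with sections 3.3 and 3.6. That conclusion rests on the wording and needs no assumed figure.

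The size is illustrative. Under LOCF, about 65 to 127 mL of decline is omitted per withdrawn patient at week 96, and the Baduanjin mean is favoured by about 6.5 to 38 mL. These figures rest on GOLD II decline rates applied to a GOLD I population, 10 to 30% withdrawn for compliance, and steady decline without early improvement. The stronger reading, that all the listed criteria remove poor performers from one arm and so certainly favour Baduanjin, goes beyond the documents.

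**What to change.** Reconcile sections 2.9, 3.3 and 3.6 as follows.
- Split section 2.9 into criteria for stopping the intervention and criteria for ending outcome measurement. The clinical criteria for stopping are not judged here and stay unchanged.
- End outcome measurement only on withdrawal of consent, death or loss to follow-up. All other randomised patients, including those who stop training, keep the scheduled visits to week 96.
- Analyse all randomised patients in the arm to which they were assigned.
- Use the 80% threshold of section 3.3 only for a supplementary adherence analysis.

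The cost is a protocol amendment, which needs renewed ethics approval under section 2.2. The visits are already scheduled. The estimate will include non-adherers and so may be smaller. Some missing data will remain through loss to follow-up. The change should be made before any patient is withdrawn under the present rule.
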